**Discussion:**

The primary goals of this research are to compare the efficacy, tolerability, and adherence of EMDR therapy plus exposure therapy and supportive counseling plus exposure therapy and to identify predictors, moderators, and mediators for treatment success. This multi-center research aims to make a significant contribution to our understanding as to how treatment for patients with anxiety disorders can be optimized, and elucidate who can benefit most from this novel approach.

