Hypotheses concerning the following secondary goals will be preregistered on the Open Science Framework [52]. The first goal is to test whether EMDR therapy + exposure therapy results in less return of fear (panic related symptoms, generalized anxiety), compared to supportive counseling + exposure therapy from posttreatment (T3) to follow up (FU1 and FU2). The second goal is to unravel predictors of optimal treatment allocation (EMDR therapy + exposure therapy > supportive counseling + exposure therapy). These include theory-driven variables (reduced extinction learning, less experienced life events, low intolerance of uncertainty, anxiety sensitivity, low worrying, enhanced imagery ability), patient variables (e.g., greater treatment credibility, better working alliance) and therapist factors (e.g., enhanced trait anxiety, better working alliance, greater treatment expectancy). The third goal is to elucidate mechanisms of change (most notably mental threat imagery, encapsulated threat beliefs) of this novel approach (EMDR therapy + exposure therapy). Finally, we will assess cost-effectiveness of the new approach (EMDR therapy + exposure therapy).

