### Recruitment

Participants will be recruited at two specialized treatment centers in the Netherlands: Mondriaan/PsyQ Academic Anxiety Center and Altrecht Academic Anxiety center. Clinicians refer patients who potentially meet inclusion criteria after a standard intake procedure. Potential participants are invited for an information session with the research assistant, who examines inclusion and exclusion criteria. After providing informed consent, baseline assessments (T1) will be made. Afterwards, participants are randomized to one of conditions (EMDR therapy + exposure therapy or supportive counseling + exposure therapy). Inclusion will continue until 50 panic disorder patients completed posttreatment (T3).

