### Sample size

For the primary objectives of efficacy, tolerability, and adherence, the sample size was calculated using G*power 3.1 [56] using a 2 (groups) × 2 (time) repeated-measures ANOVA. Given the active control condition, we expect a medium effect size [9]. For a between group effect size of f = 0.25, alpha 0.05, power 0.80, 0.5 correlation among repeated measures and 1.0 non-sphericity correction, a total sample size of 98 participants is needed for two-sided testing. Although no formal method is available to determine a repeated-measures ANOVA sample size using Bayesian statistics, approximations for t-test are available [57]. For a one-sided *t*-test with a power of 0.80 and a Bayes factor of 3 (indicating evidence for the data coming from the alternative than the null hypothesis), 87 participants are needed and for a Bayes factor of 5, 99 participants are needed. Originally, we aimed to recruit 100 participants (see pre-registration: ISRCTN - ISRCTN29668369). However, the COVID-19 pandemic has seriously impacted the number of referrals of patients with panic disorder. To increase the feasibility of the study, we formulated directional hypotheses and decided to use one-sided testing, which reduces our sample size to 50 participants [58]. This change was approved by the ethical committee on February 8 2023. Participants who will not show up to therapy sessions in the first two weeks of treatment will be considered non-compliant and will be described as dropouts. Dropouts will not be excluded from intent to treat analyses, but will be replaced by additional participants to preserve statistical power. The completer sample size will be sufficient to address secondary objectives.

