Secondly, we expect to recruit a culturally and socioeconomically diverse sample. No strict exclusion criteria are used and clinics are in large cities across the Netherlands, which enhances the external validity of our results [119, 120]. Given that dropouts are common in this population [11–14], we will use an intention to treat analysis. Reasons for dropout will be monitored as attrition rates are an important outcome measure in this study. Validity of the trial is further improved by using standardized measures and by letting the assessments being conducted by researchers blind to treatment condition. Furthermore, the sample size should provide sufficient power for the primary- and secondary aims to enable meaningful conclusions.

Researcher allegiance bias is problematic in psychotherapy research [121, 122], including studies about EMDR therapy efficacy in anxiety disorders [38, 40]. Therefore, we follow recommendations to reduce research allegiance bias, such as having a collaborative team with mixed allegiances [121]. Study therapists are trained and supervised for the same amount of time for all treatment conditions, and treatment integrity will be checked [123]. To reduce expectancy biases in patients and clinicians a strong rational for all treatments, including supportive counselling, is provided. Furthermore, we use identical procedures (including EMDR-case conceptualization) and treatment duration between conditions. Treatment credibility and expectancy for all treatments are monitored for all patients and study-therapists.

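### Power is claimed for the secondary aims, but 50 completers are too few for the drop-out comparison and for treatment-by-predictor (optimal allocation) analyses

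*Protocol article*

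**What the plan says.** Two sentences in the protocol article assert adequacy. The Discussion, in its list of design strengths, says that "the sample size should provide sufficient power for the primary- and secondary aims to enable meaningful conclusions". The Sample size section ends with "The completer sample size will be sufficient to address secondary objectives".

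The aims they cover include:
- Drop-out. Hypothesis 3 (Goals of the current study) predicts less actual drop-out after EMDR therapy, and the Discussion calls attrition an important outcome.
- Optimal allocation. "The second goal is to unravel predictors of optimal treatment allocation", with a list of patient and therapist variables. The Abstract restates the ambition as "to identify predictors, moderators, and mediators for treatment success".
- Mechanisms of change (the third secondary goal, listed under Instruments as goal 3).

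The only power calculation is in Sample size. It begins "For a between group effect size of f = 0.25, alpha 0.05, power 0.80", with a correlation of 0.5 between repeated measures in a 2 × 2 repeated-measures ANOVA, and concludes that "a total sample size of 98 participants is needed for two-sided testing". For feasibility the investigators then "decided to use one-sided testing, which reduces our sample size to 50 participants". The Recruitment section counts completers at T3 towards the 50. Sample size says that dropouts are replaced and stay in the intention-to-treat analysis. The Limitations section does not mention power.

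**The concern.** The two sentences state a property of the design, and no calculation in the article supports it for drop-out, moderators or mediators. Comparing arms on drop-out, and asking which patients do better on which arm, both usually need far larger samples than a main-effect comparison. If power is low, a null drop-out result says little and an apparent moderator may be a chance or exaggerated finding. A published assurance of sufficient power invites the opposite reading: the null taken as equivalence, and the moderator taken as a guide to treatment choice.

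**Working it through.** **1. The article's own calculation.** Inputs from Sample size: f = 0.25, m = 2 measurements, ρ = 0.5, α = 0.05, power 0.80. For the between-group effect, λ = f²·N·m / (1 + (m − 1)ρ), with an F test on 1 and N − 2 degrees of freedom.
- N = 98: λ = 0.0625 × 98 × 2 / 1.5 = 8.17, two-sided power 0.808. The stated 98 is reproduced.
- N = 50: λ = 0.0625 × 50 × 2 / 1.5 = 4.17. Power is 0.516 two-sided and 0.643 one-sided (F test at α = 0.10).
- One-sided 80% power needs N = 76.

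So 50 does not follow from the stated inputs, even for the effect that was sized.

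**2. Drop-out.** The Background gives 10–20% drop-out in general; the article sets no target difference. The differences below are therefore assumptions. Power is by exact binomial enumeration, one-sided 5%; the lower figure is Fisher's test and the higher is the score test.

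| Drop-out | 25 per arm | 31 per arm |
|---|---|---|
| 20% vs 10% (upper rate halved) | 16–27% | 17–31% |
| 20% vs 5% | 33–52% | 38–61% |
| 30% vs 10% | 45–57% | 51–66% |

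The 31 per arm allows for replaced dropouts: 50 completers at 20% loss means 50 / 0.8 ≈ 62 randomized. A Poisson log-rate test, closer to the count model named in Data analysis, gives 23% for 20% versus 10% with 25 per arm. By the normal approximation, 80% one-sided power for 20% versus 10% needs 157 per arm.

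**3. Treatment-by-moderator interaction.** Assume a standardised moderator, 1:1 allocation and N = 50. The standard error of the interaction slope is 2σ/√N, where σ is the residual SD in outcome SD units.
- Unadjusted, σ = 1: SE = 2/√50 = 0.283. Detectable slope at 80% one-sided power = (1.645 + 0.842) × 0.283 = 0.70 SD per moderator SD.
- Adjusted for baseline with correlation 0.5, σ = √(1 − 0.25) = 0.866: SE = 0.245. Detectable slope = 2.487 × 0.245 = 0.61.
- With about 62 analysed, the same two figures are 2.487 × 2/√62 = 0.63 and 0.866 × 0.63 = 0.55.

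The planned treatment effect is d = 2f = 0.5 SD, so every version exceeds it. A true slope of 0.25 has 22% power unadjusted and 27% adjusted. A slope of 0.50 has 55% and 65%. With a balanced binary moderator and subgroup effects differing by d = 0.5, SE = 4/√50 = 0.566 and one-sided power is 22%.

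**4. Mediation.** No power was calculated here and the article shows none.

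**The case against.** The strongest reply is that the article sets no target for these aims, so any power figure depends on what one assumes, and that analyses for goals 2–4 are deferred to preregistration. Both points are true. But an unqualified claim of sufficiency is made now, and later preregistration does not supply its missing basis.

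Other parts of the reply stand and limit the point:
- Not every secondary aim is badly powered. A simple prognostic correlation of 0.3 in 50 patients has 56% (two-sided) to 68% (one-sided) power, and an interaction of f² = 0.15 has 77% to 85%. The continuous symptom scales have 52% to 64% under the article's between-group model. They would have 93% to 97% if f = 0.25 were read as a group-by-time effect, but that reading needs only 34 patients two-sided and does not give the stated 98.
- Sample size places tolerability and adherence under the primary objectives, so "The completer sample size will be sufficient to address secondary objectives" may refer only to goals 2–4. The Discussion sentence covers primary and secondary aims alike, so the drop-out criticism holds under either label.
- The Discussion sentence is hedged with *should*.

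A reader might also infer four stronger things that the documents do not support:
- That the claims were written for 100 patients and never revised. The article records the cut from 100 to 50 but shows no earlier text of these sentences.
- That refusal of exposure (25–30% in the Background) is an underpowered binary endpoint. Willingness is a 0–100 visual analogue scale.
- That about ten predictors tested at 5% give a 40% chance of a false one (1 − 0.95¹⁰ = 0.40). This presumes independent, uncorrected tests, and the article leaves that plan to preregistration.
- That mediation is shown to be underpowered. It is only unsupported.

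**Conclusion.** The point holds for the drop-out comparison and the treatment-by-predictor analyses. Under every drop-out difference in the table, including a fall from 30% to 10%, one-sided power stays well below 80%, whether 25 or 31 per arm are counted. A moderator must shift the treatment effect by more than the whole planned effect, per SD of the moderator, to be detected with 80% power.

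These figures rest on assumed drop-out differences, 1:1 allocation, one-sided 5% tests (the more favourable choice) and, for the lower interaction figure, baseline adjustment at the stated correlation of 0.5. For mediators the conclusion is only that adequacy is asserted without support. The documents do not support a claim that all secondary aims lack power. This is a correction that should be made, and it leaves the design and the data collected unchanged.

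**What to change.** Withdraw or qualify the two sufficiency sentences in Sample size and Discussion. In their place:
- State what 50 completers can detect, with the assumptions attached: for example, an interaction of about 0.6 SD (baseline-adjusted, correlation 0.5) to 0.7 SD (unadjusted) per moderator SD at 80% one-sided power, and the power for a named drop-out difference on the number expected to be randomized. Do not present any one figure as an assumption-free limit.
- Label the drop-out comparison, the moderator analyses (goal 2) and the mediator analyses (goal 3) as exploratory, and report them as estimates with 95% confidence intervals.
- State that no treatment-allocation conclusion, and no conclusion of no difference, will be drawn from them.
- Add the limited power to the Limitations section.

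The cost is wording only. No procedure, sample or measurement changes, but the stated claims become less favourable.

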### Limitations

No waiting list control group is used, which could be considered a limitation [124, 125], given that it can serve as a valuable benchmark in pilot studies for a new intervention [123], but it is not necessary in this study for at least four reasons. First, effect sizes for EMDR therapy, supportive counseling and CBT in anxiety disorders have already been established [9, 38, 40], so a benchmark is not needed and could artificially inflate effect sizes [126, 127]. Second, it could also result in unwanted nocebo effects [125, 128, 129]. Third, it can create ethical dilemmas [125, 130] and potentially raise the threshold to participate in a trial resulting in selection bias [127, 131]. Finally, it can reduce study or treatment satisfaction [127, 132] which may influence attrition rates [132].

Furthermore, no direct comparison between EMDR therapy and exposure therapy is made [123]. However, instead of finding a substitute for exposure, we aim to improve it beyond common factors by studying mechanisms of action. So, the question whether EMDR therapy is more effective compared to exposure therapy is beyond the scope of this study.

Although knowledge of the long-term effects of CBT is urgently needed [16, 18] only a six month instead of a one- or two-year follow-up measurement is included. After follow-up 1 (FU1; one-month posttreatment) patients will receive additional treatment if needed (also for co-morbid disorders), as we aim to include a representative sample. Therefore, long-term effects can not solely be attributed to the trial interventions. We could not circumvent this issue due to ethical considerations.

Finally, as this study is an efficacy trial, highly trained and supervised professionals provide the treatment, therefore effectiveness research is still needed after the trial [133]. To promote the dissemination of the results a treatment protocol will be published separately.

To recapitulate, many anxiety patients do not profit sufficiently from CBT, underlining the urgent need for treatment optimization. Threat-related imagery may play a maintaining role in the disorder or impede exposure therapy. Currently, imagery (especially future-oriented) is not targeted in standard CBT for anxiety disorders. Therefore, we aim to assess whether EMDR therapy with exposure therapy, relative to supportive counseling with exposure therapy, improves treatment efficacy, tolerability, and adherence in patients with panic disorder. The results of this study may have important clinical implications for the treatment of patients with anxiety disorders, as well as a better understanding of the mechanisms of action paving the way to personalized medicine.

### Trial status

Currently recruiting participants.

### Protocol version

Version 1: original, issue date 26–08-2020. Version 2: amendment adding treatment integrity (video recordings), issue date 26–05-2021. Version 3: amendment changing information letter and adding time stamps in questionnaire response, issue date 27–07-2021. Version 4: amendment to 1) reduce the sample size for panic disorder from *N* = 100 to *N*= 50 to enhance feasibility of the study and adapting statistical analyses accordingly (one-sides testing instead of two sided testing), 2) terminate a RCT in social anxiety disorder, due to a low influx of participants, 3) the option for participants not to consent with audio and video recordings, 4) change the session frequency (once instead of twice weekly), 5) stopping the Experience Sampling Measurements, 6) enable videoconferencing aside from the pandemic restrictions, 7) report the study progress, issue date 08-02-2023.

## Data Availability

To promote open science, this trial is retrospectively registered ISRCTN—ISRCTN29668369: Improving anxiety treatment by modifying emotional memories before real-life exposure including the (main) hypotheses. Materials (in Dutch) used in the study as well as all the articles that are a product of this trial will be made available after trial completion in the trial registry. The World Health Organization trial registration data set guidelines (SPIRIT guidelines) will be used to register the data set [134, 135]. To promote data quality, a secured data base (REDCAP) will be used [53, 54]. For further details about data storage and security, see the original IRB-proposal. Data sharing for this study is not applicable yet, because no datasets have so far been generated or analyzed.

## Abbreviations

ASI: Anxiety Sensitivity Index
ATPTM: Attitudes Toward Psychotherapy Treatment Manuals
BSQ: Bodily Sensation Questionnaire
CBT: Cognitive behavioral therapy
CEQ: Dutch credibility and expectancy scale
CS: Credibility Scale
CSQ-8: Client Satisfaction Questionnaire
EBPAS: Evidence-Based Practice Attitude Scale
EMDR: Eye movement desensitization and reprocessing
EQ-5D: EuroQol
FQ-A: Fear Questionnaire-Agoraphobia
FU(nr.): Follow up
GAD-7: General Anxiety Disorder 7
IES: Impact of past event scale
IFES: Impact of future event scale
IUS: Intolerance of Uncertainty Scale
LMM: Linear Mixed Models
LTE: List of Threatening Events
MINI-S-DSM-5: Mini-International Neuropsychiatric Interview-Simplified for DSM-5
MLR: Mixed Logistic Regression
NPS: Net Promotor Score
Nr.: Number
PAS: Panic Agoraphobia Scale
PDSS-R: Panic Disorder Severity Scale- self-report form
PHQ-9: Patient Health
PSWQ: Pen State Worry Questionnaire
PTOS: Predicting Treatment Outcome Survey
REDCAP: Research Electronic Data Capture
SAFE-A: Subtle Avoidance Frequency Examination – agoraphobia
SAM: Survey of Autobiographical Memory
SUD: Subjective unit of distress
T(nr.): Assessment
TIC-P: Treatment Inventory of Costs
VAS: Visual Analogue Scales
VOC: Validity of cognition
WAI-12: Working Alliance Inventory
WIMI: Waterloo Images and Memories Interview
WSAS: Work and Social Adjustment Scale
